## Abstract

**Background:**

Despite improvements in treatments, head and neck cancer survivors (HNCS) still endure acute and chronic side effects such as loss of muscular strength, limitations in physical function, fatigue, and swallowing difficulties that impact quality of life (QoL). Light-to-moderate intensity strength training (LMST) has been shown to improve some of these side effects. Heavy lifting strength training (HLST) may further improve outcomes, however, only one pilot study has focused on HNCS. The primary aim of this study is to further establish the feasibility of HLST in HNCS. A secondary aim is to provide preliminary evidence of the effects of a HLST program compared to Usual Care (UC) in HNCS.

**Methods:**

This single-centre, two-armed, randomized controlled trial will aim to recruit 48 HNCS ≥1-year post-treatment, and randomly assign them to a 12-week Heavy Lifting Strength Training (HLST) group or Usual Care (UC) group. With 80% power, a two-tailed alpha of p < 0.05, and adjusting for covariates that explain 25% of the variance in the outcome, we will be able to detect a standardized effect size of 0.80 with 38 (19/group) evaluable HNCS, allowing for a 20% loss to follow-up. The HLST group will exercise twice weekly, progressing to lifting low repetitions of heavy loads at 80% to 100% of maximal perceived exertion, whereas the UC group will not receive any exercise prescription or instruction during the 12-week intervention. The primary efficacy outcome will be upper and lower body muscular strength assessed by 3RM tests. Secondary efficacy outcomes will include health-related fitness and patient-reported outcomes assessed with reliable physical assessments and validated questionnaires.

**Significance:**

Our findings will answer the important question of whether lifting heavier weights is feasible for HNCS and leads to better outcomes compared to lifting no weights. The results will inform future studies comparing exercise intensities in HNCS and other cancer populations.

## Introduction

Head and neck cancers (HNCs) are complex and diverse tumours, originating in the oral cavity, oropharynx, hypopharynx, nasopharynx, lip, larynx, paranasal sinus, salivary gland, and mucosal melanoma [1]. HNCs are in the top 10 most common cancers worldwide, and make up approximately 5% to 7% of solid tumours globally [2–6]. Standard treatment for early stage HNC is surgery or radiotherapy. Multiple modalities, mainly chemoradiotherapy, are used for locally advanced HNC [7]. Despite improvements in treatments, head and neck cancer survivors (HNCS) still endure numerous acute and chronic side effects including: dental and oral complications, nutritional, speech and voice impairments, immune suppression, infectious complications, shoulder dysfunction, pain, shortness of breath, reduced muscle strength and mass, physical fatigue, difficulty sleeping, swallowing dysfunction and affected appetite, self-consciousness, embarrassment unattractiveness, low self-esteem, and reduced quality of life (QoL) [7–15].

Strength training improves some of these side effects in HNCS [16–22], however, most studies to date have tested light to moderate strength training (LMST) rather than training with heavy loads [14,16,17,20,22–25]. LMST involves lifting lighter loads more times (i.e., 10–15 repetitions) whereas heavy lifting strength training (HLST) involves lifting heavier loads fewer times (i.e., 1–6 repetitions), typically, 80% to 100% of one repetition maximum (1RM) [26]. While LMST interventions have been shown to be beneficial for HNCS, preliminary HLST research in HNCS and other populations have shown that training with heavy loads may be feasible and necessary in order to maximize muscular strength gains [26–28]. These findings are promising and raise the question on whether or not HLST may lead to greater improvements in skeletal muscle mass, strength, and function, and QoL in HNCS.

Here, we propose the Feasibility and Preliminary Efficacy of Heavy Lifting Strength Training versus Usual Care in Head and Neck Cancer Survivors (the LIFTING 2) trial, the first phase II, randomized controlled trial that will further establish the feasibility of HLST using free weights, and provide preliminary efficacy data compared to Usual Care (UC) in HNCS. The primary efficacy outcome is upper and lower body muscular strength changes from baseline to post-intervention, assessed by reliable 3 repetition maximum (3RM) tests. Secondary efficacy outcomes include physical function, shoulder mobility, and handgrip strength assessed by validated physical assessments; body composition components such as skeletal muscle mass and body fat percentage assessed by bioelectrical impedance; and quality of life (QoL), fear of cancer recurrence, symptom burden, fatigue, self-esteem, sleep, swallowing abilities, and nutritional status assessed by well-validated questionnaires. We hypothesize that HLST will be safe and feasible for HNCS, and anticipate no adverse events to occur which are directly related to HLST [28–30]. Lasty, we expect that HLST will be superior to UC for muscle strength, mass, and function, and QoL.

## Methods

### Study design

The LIFTING 2 trial will be conducted as a single-centre, two-armed, phase II, randomized controlled trial at the University of Alberta in Edmonton, Alberta, Canada. Participants will be randomly assigned to the 12-week HLST or UC group. Participants will be stratified based on sex and cancer stage (I-III vs. IV). The proposed flow of participants in the LIFTING 2 trial is summarized in **Fig 1**.

**Fig 1 pone.0326860.g001:**
[figure not shown]
CONSORT flow diagram.

### Study population

Eligible participants will include males and females who meet the following criteria: 1) any HNC subtype, cancer stage (I-IV), and treatment type (i.e., surgery, chemotherapy, radiation, combination treatment); 2) at least one-year post-treatment of any kind with adequate shoulder range of motion (active flexion and abduction) or recovery of the spinal accessory nerve (SAN); 3) 18 years and older; 4) no unmanaged medical conditions; 5) approved for exercise by oncologist and a certified exercise physiologist or kinesiologist; 6) ability to understand and communicate in English; 7) has not met the Canadian Physical Activity strength training guidelines within the past one-month: *at least two days per week of muscle and bone strength training activities using major muscle groups*. and 8) participants will be excluded if they are currently involved in a different exercise trial or clinical drug trial. Our target accrual number is 48 patients over 12-months. Participant recruitment and data collection will begin in March 2025 and end in March 2026. Results will be collected on an ongoing basis during this timeframe, but will be analyzed and interpreted between April and June 2026. See **Table 1** for a schedule of enrollment, interventions, and assessments.

**Table 1 pone.0326860.t001:** Timeline of enrollment, interventions, and assessments for the LIFTING 2 Trial.

	STUDY PERIOD				End of Study
	Enrollment	Allocation	Post-Allocation		
TIMEPOINT	Baseline	0 weeks	6 weeks	12 weeks	Wrap-Up

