### Randomization and blinding

After completing baseline assessments, participants will be randomly assigned to either the HLST Group or the UC Group in a 1:1: ratio using a computer-generated program within REDCap, with random blocks of 4 or 6. The allocation sequence will be generated by and independent researcher and uploaded directly to REDCap to ensure concealment from study personnel. Participants will be stratified by biological sex and cancer stage (I-III vs. IV) to ensure balanced group distribution. Additional stratification variables will be considered in a future phase III trial. The UC Group was chosen as the comparator in order to evaluate the feasibility and efficacy of a HLST program. During the conception of this study, we considered comparing HLST to LMST but felt that we needed to further establish the feasibility of HLST before comparing it to LMST. A future phase III study would then compare HLST to LMST to determine the optimal exercise intensity for HNCS.

Group allocation will be shared with the participant immediately after the baseline assessment. Participants and investigators will not be blinded to group assignment, given the nature of the intervention. Outcome assessors will also not be blinded to group assignment because of logistical challenges. However, we will follow a standardized, detailed protocol and all assessors will be trained on the importance of standardizing outcome assessments and prioritizing safety.

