Participants that are randomized to the UC group will be asked to continue with their typical daily routine and habit of exercise during the 12-week intervention period. They will not receive any information or education regarding exercise. After the post-intervention assessments at 12-weeks, the UC group will be offered a 4-week introduction to HLST program and/or referred to a community-based exercise program.

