### Sample size

Our goal will be to recruit 48 HNCS. With 80% power, a two-tailed alpha of p < 0.05, and adjusting for covariates that explain 25% of the variance in the outcome, we will be able to detect a standardized effect size 0.80 with 38 (19/group) evaluable HNCS allowing for a 20% loss to follow-up. We believe that this large effect on strength is realistic in our study, given that we are comparing HLST to no exercise. Additionally, all participants would not have participated in any sort of strength training within at least the past one-month. As it is difficult to power a feasibility trial on the feasibility outcomes, we have powered the trial on the first indicator of efficacy, which is muscular strength. Our study is approaching all HNCS in the Edmonton and surrounding area. Therefore, there is no viable secondary plan if the target accrual is not reached. Based on an initial review by the Alberta Cancer Registry, there are approximately 1,495 HNCS living in the Edmonton area. Based on our previous studies [13,14,20–22,25,28,52,53], we expect around 50% to be eligible and a recruitment rate of about 6%, which will allow us to reach our target.

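### Twelve months of accrual plus a 12-week outcome cannot fit between March 2025 and March 2026, and no last-randomisation or last-assessment date resolves it

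*Protocol article*

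**What the plan says.** The Study population section of the protocol article sets the accrual period: "Our target accrual number is 48 patients over 12-months". The next sentence gives recruitment and data collection one shared window: "Participant recruitment and data collection will begin in March 2025 and end in March 2026". Results then "will be analyzed and interpreted between April and June 2026".

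The Introduction defines the main efficacy measure: "The primary efficacy outcome is upper and lower body muscular strength changes from baseline to post-intervention". The 12 weeks start after baseline, because the Randomization and blinding section says "After completing baseline assessments, participants will be randomly assigned to either the HLST Group or the UC Group". The Intervention section places the closing test at 12 weeks in the control arm as well: "After the post-intervention assessments at 12-weeks, the UC group will be offered a 4-week introduction to HLST program". Table 3 labels the same visit as 3 months.

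The Sample size section asks for 38 evaluable participants (19 per group) and recruits 48 to allow for 20% loss. The Statistical considerations section uses complete cases below 10% missing data and multiple imputation above 10%. No section gives a date for the last randomisation or the last 12-week assessment.

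**The concern.** Anyone randomised less than 12 weeks before data collection closes cannot have a post-intervention strength test within the stated period. A trial that accrues for a full 12 months and closes both activities together has such participants by construction, unless accrual finishes early.

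Three things are at stake. The first is the number evaluable for the outcome on which the trial is powered. The second is the missing-data rule, which calendar losses alone could trigger. The third is the reading of feasibility, the primary aim: the follow-up assessment rate is a feasibility outcome, and failure to recruit 48 is a listed threshold. A shortfall caused by the calendar could be mistaken for a problem with the intervention.

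**Working it through.** **Inputs from the protocol article.** Accrual is 48 over 12 months, or 4 per month. The window is March 2025 to March 2026, with no days given. Follow-up is 12 weeks (84 days). The effect is 0.80 SD, covariates explain 25% of the variance, alpha is 0.05 two-sided, power is 80% and loss is 20%.

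**Assumptions, not in the article.** Accrual is uniform over 365 days. Data collection stops on the closing date. The full 20% loss applies on top of any calendar loss.

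**The plan's own figure.** Residual SD = √(1 − 0.25) = 0.866. By the normal approximation, n per group = 2 × (1.960 + 0.842)² × 0.75 / 0.80² = 18.4, rounded up to 19, so 38 in total. Then 38 / 0.8 = 47.5, rounded up to 48. The stated sample size reproduces. Power at 19 per group is 81% by the normal approximation and 79% by the noncentral t with one covariate degree of freedom.

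**Does the calendar fit?** 365 + 84 = 449 days, and 449 / 30.44 = 14.8 months. The longest possible window, 1 March 2025 to 31 March 2026, is 395 days, or 13.0 months. No choice of days in March fits.

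**Participants without a 12-week visit if accrual runs the full 12 months**

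| Days in March | Accrual days too late | Affected, of 48 | Reach 12 weeks | After 20% loss |
|---|---|---|---|---|
| 1 March 2025 to 31 March 2026 (most favourable) | 365 − 311 = 54 | 54/365 × 48 = 7.1 (15%) | 40.9 | 32.7 |
| Same day in both years | 84 | 84/365 × 48 = 11.0 (23%) | 37.0 | 29.6 |
| 31 March 2025 to 1 March 2026 (least favourable) | 365 − 251 = 114 | 114/365 × 48 = 15.0 (31%) | 33.0 | 26.4 |

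The 311 and 251 are the days from the start to 84 days before close (395 − 84 and 335 − 84). Every row exceeds the 10% missing-data limit before any dropout.

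**Power.** The noncentrality is (0.80 / 0.866) × √(n/2), with n per group. On the noncentral-t scale, 30 evaluable (15 per group) gives 68%, 33 (16.5 per group) gives 73%, and the unaffected 38 gives 79%. By the normal approximation the first two rows give 71% and 75%, against 81%.

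**If randomisation stops 84 days before close.** The last randomisation falls between 7 December 2025 (close on 1 March) and 6 January 2026 (close on 31 March). That leaves 281/30.44 = 9.2 months of accrual with the same day in both years, and 8.3 to 10.2 months across all choices of days. At 4 per month, 9.2 to 10.2 months gives about 37 to 41 randomised, and the least favourable days give 33. Reaching 48 needs 48/9.2 = 5.2 per month (4.7 to 5.8).

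**If 12 months of accrual is kept.** The last 12-week assessment falls between 24 May 2026 (start on 1 March 2025) and 23 June 2026 (start on 31 March 2025). Both dates lie inside the planned analysis period.

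**The case against.** The strongest defence is that March to March is an overall study window, given only to the month, in which the last enrolment naturally precedes the last assessment. Nothing in the article says that randomised participants will be cut off. The Statistical considerations section even invites those who withdraw to complete follow-up, so the likelier result is slippage and not missing outcomes. Recruitment is by registry contact of all potentially eligible survivors, which could fill the trial early. If 48 were reached by December 2025 or early January 2026, nobody would be affected.

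Much of this stands. The loss of outcomes is conditional, and the counts depend on an accrual pattern that the article does not give. The power figures should be set against 79% on the same scale, not the stated 80%. The primary aim is feasibility, and the Discussion already accepts a low likelihood of statistical significance.

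The defence does not remove the conflict. Stopping recruitment in December or January contradicts 12 months of accrual, and late visits contradict the March 2026 close and overlap the analysis period.

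A reader might infer that, whichever way the conflict is settled, neither the 38 evaluable participants nor the follow-up rate can be delivered. The article does not support that. Stopping randomisation 12 weeks early leaves the follow-up rate intact and still reaches 48 at about 5.2 per month. Even at the unchanged pace, 41 randomised would yield 38 evaluable if loss stayed at or below about 7% (1 − 38/41). The 20% is a planning allowance.

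**Conclusion.** The point holds as an internal contradiction in the timeline: about 14.8 months of activity is placed in at most 13. That conclusion needs no assumption about accrual.

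The consequences are conditional. With uniform accrual over 12 months and a hard close, about 7 to 11 of 48 lack the primary outcome. The range widens to about 15 on the least favourable days in March and to none if accrual is front-loaded. With the full 20% loss added, the 7 to 11 case leaves about 30 to 33 evaluable and noncentral-t power of about 68% to 73%, against 79%. With an early stop at the unchanged pace, the cost is recruitment (about 37 to 41 randomised), not follow-up.

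The sample size calculation is sound. Only the calendar needs correcting, and it should be corrected because the recruitment and follow-up rates are themselves feasibility results.

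**What to change.** Give recruitment and data collection separate end dates in the Study population section, in one of two ways.

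- **Keep the March 2026 close.** State a last-randomisation date at least 12 weeks earlier (between about 7 December 2025 and 6 January 2026, depending on the closing day). Replace 48 over 12 months with the accrual rate this implies, about 5.2 per month (4.7 to 5.8). The cost is a faster accrual target.
- **Keep 12 months of accrual.** End data collection after the last 12-week assessment, about late May to late June 2026 depending on the start day, and move analysis after it. The cost is about three more months before analysis.

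Either change is a timeline edit. The sample size, randomisation and analysis method stay as they are.

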**ENROLLMENT**					
Eligibility Screening	X				
Informed Consent	X				
Questionnaires	X				
Baseline Assessment	X				
Randomization		X			
**INTERVENTIONS**					
Heavy Lifting Strength Training					
Usual Care					
**ASSESSMENTS**	X				X

### Recruitment and screening

Potentially eligible participants will be identified and contacted via the Alberta Cancer Registry, a database that holds information pertaining to all living and deceased individuals diagnosed with cancer in the province of Alberta, Canada. By recruiting in this way, we will have contacted all potentially eligible HNCS at least one-year post-treatment.

Interested HNCS will contact and meet with the study coordinator ([name]) via an online pre-screening meeting, which will serve as a chance to ask about medical history such as type of cancer, cancer stage, and treatment type, elaborate further on study details, and obtain verbal informed consent at this time. Once online questionnaires are complete in the Research Electronic Data Capture (REDCap), and the study coordinator will schedule interested HNCS for in-person baseline physical assessments at the Exercise Oncology Research Laboratory at the University of Alberta. Finally, eligibility will be determined through objective measurements of active shoulder flexion and abduction ranges of motion. To satisfy eligibility criteria #2 above, participants will be required to meet or exceed the following age-based cut points for shoulder range of motion: participants 18–50 years old: ≥ 150° for flexion and abduction; participants over 50 years old: ≥ 130° for flexion and abduction.

### Randomization and blinding

After completing baseline assessments, participants will be randomly assigned to either the HLST Group or the UC Group in a 1:1: ratio using a computer-generated program within REDCap, with random blocks of 4 or 6. The allocation sequence will be generated by and independent researcher and uploaded directly to REDCap to ensure concealment from study personnel. Participants will be stratified by biological sex and cancer stage (I-III vs. IV) to ensure balanced group distribution. Additional stratification variables will be considered in a future phase III trial. The UC Group was chosen as the comparator in order to evaluate the feasibility and efficacy of a HLST program. During the conception of this study, we considered comparing HLST to LMST but felt that we needed to further establish the feasibility of HLST before comparing it to LMST. A future phase III study would then compare HLST to LMST to determine the optimal exercise intensity for HNCS.

Group allocation will be shared with the participant immediately after the baseline assessment. Participants and investigators will not be blinded to group assignment, given the nature of the intervention. Outcome assessors will also not be blinded to group assignment because of logistical challenges. However, we will follow a standardized, detailed protocol and all assessors will be trained on the importance of standardizing outcome assessments and prioritizing safety.

### Maximal strength testing

Two separate 3RM tests will be used for baseline and post-intervention physical assessments to evaluate upper and lower body strength with the leg press and chest press machines. Maximal testing is safe, reliable, and the gold standard for assessing muscle strength in healthy, older adults [31]. Prior to attempting these movements, the study coordinator will give an in-depth explanation of the purpose of the tests, how to safely execute the lifts, and a demonstration.

To begin, after a 5-minute aerobic warm up and standardized dynamic stretches, study participants will perform bodyweight and resistance band movements to practice appropriate technique. Progressions leading up to the 3RM are as follows. For the leg press, participants will initially perform 8–10 reps at less than 50% of body weight in pounds. To follow, the reps will decrease as the weight gradually increases based on body weight in pounds: 50% body weight for 5–6 reps, 70% for 2–3 reps, and 85%, 90%, 95%, and 100%+ for 3 repetitions. For the chest press, after warming up with a resistance band, participants will perform 8–10 reps at less than 35% of body weight in pounds. Following this, the reps will also decrease as the weight gradually increases based on body weight in pounds: 35% body weight for 5–6 reps, and 40%+ for 3 reps. 3RM tests will be performed in this order: leg press, followed by chest press.

In order to assess a true 3RM, the following factors will be considered. Since the Borg RPE Scales are primarily used to assess intensity of aerobic exercise and may be inaccurate and difficult to conceptualize for beginner lifters [32], a repetition in reserve (RIR)-based RPE scale will be used to assess exercise intensity, which may be more valid to assess maximal or near maximal strength than RPE alone [32]. After each set during the physical assessments, participants will be asked for their RPE, which corresponded to a number on the RIR scale. Participants will be asked the following question, “If I didn’t stop you, how many more repetitions could you have done after the prescribed number?” Conversions from RPE to RIR are as follows: RPE 10 = RIR 0 (maximum effort), RPE 9 = RIR 1, RPE 8 = RIR 2…RPE 1 = RIR 9+ (little to no effort) (44). For maximal testing, participants should report an RIR of 0–1, or RPE of 9–10, in order for the lift to be considered a true maximal test.

In addition to the RIR-based RPE reports, the study coordinator will assess 3RM tests via observation. As the weight increases and the reps decrease while approaching a 3RM, time under tension (total duration of lift) should be progressively longer. Participants should be somewhat struggling to move the weight when a true 3RM has been reached, and should not be able to quickly move the load. If the latter was the case and participants do not want to continue for whatever reason, the reps and load will be plugged into a 3RM prediction equation, and this maximal testing limitation will be recorded.

Finally, attention will be paid to form for both 3RM tests. Participants should maintain the same leg press squat depth even as loads increase, although there is a tendency to shorten range with increasing weight, making the lift easier and shorter in duration (less time under tension). To avoid this issue and maintain consistency in squat depth across all participants, the number at the side of the leg press machine (indicating its depth) will vary between participants and be recorded. This depth will remain the same for baseline and post-intervention assessments for each participant. Lifters will begin in a deep enough position so that the knee joint forms a 90-degree angle. From here, they will push and the starting position will be in the extended position. Lifters will be instructed to squat down by hinging at the hips and bending the knees, until the weight plates come close to each other, then push back up. If the leg press range is shortened with increasing weight, the lifter will be reminded to bring weight plates closer by sinking down deeper with a greater bend in the knees and hip hinge. They will be stopped if the same form and depth cannot be maintained with increasing load.

For the chest press assessment, the seat height for each participant will vary and be recorded. This height will remain the same for baseline and post-intervention assessments to maintain consistency. Lifters will hold onto the vertical handles and push, starting in an extended position. With a neutral wrist, they will then be instructed to lower the weight by bending at the elbows, until the weight plates come close to each other and upper arm is in line with the torso’s midline, then push back up. If the chest press range is shortened with increasing weight, the lifter will be reminded to bring weight plates closer to each other by extending at the shoulder, allowing elbows to sink further back. They will be stopped if the same form cannot be maintained with increasing load.

